#### Strategies to improve adherence

The two main reasons for investigators to deviate from trial protocol are the occurrence of hemodynamic instability and refractory hypoxemia. So, during the pre-op visit, patients at risk for massive bleeding and hemodynamic instability should be identified. In addition, patients should be screened for risk factors of hypoxemia during one lung ventilation.Protocol amendments.

The primary investigator would notify all members of the research team, the ethics committee, and the surgeons, nurses and other anesthesiologists of our center who provide assistance to the implementation of the trial. After notification, a copy of the revised protocol would be added to the investigator site file.

#### Trial steering committee

The trial steering committee composes of colleagues of our department who supervise the progress of the trial and the integrity of collected data as well as anesthesiologists experienced in thoracic surgery anesthesia who provide valuable advice when unexpected adverse events arise. The trial steering committee meets every six months.

### Study endpoints

The primary endpoint of the study is oxygenation index: before induction (T0), after intubation (T1), after adjustment of the position of the double lumen tube in lateral decubitus position (T2), 5 min after PEEP titration and before pleura opening (study group) and 5 min after ventilating in lateral decubitus position (control group) (T3), after achieving satisfactory collapse of the independent lung (lung collapse index reaching 8 [13]) (study group) and 5 min after completing iPEEP titration and achieving satisfactory collapse of the independent lung (control group) (T4), before resuming two lung ventilation (T5).

Secondary endpoints are as follows:Results of blood gas analysis.Qs/Qt (intrapulmonary shunt) (calculated with results of blood gas analysis obtained at each time point).Respiratory parameters (tidal volume (TV), respiratory rate (RR), plateau pressure (Pplat), static lung compliance (Cstat), driving pressure ($$\Delta$$ P)) recorded at the following time points: before and after RM, each step of iPEEP titration, before and after pleura opening, once every 15 min after pleura opening, before and after resuming two lung ventilation, before and after patients are turned into supine position at the end of surgery, before extubation.Anesthesia-associated parameters: hemodynamic parameters, incidence as well as total duration of hypotension, time required for emergence from anesthesia, dose of anesthetics, incidence, and total duration of hypoxemia.Hygienic indicators: incidence of transference to ICU, length of ICU stay, length of hospital stay, and adverse events.PPCs. We define PPCs as follows:Respiratory infection: Two or more of the following for > 48 h: new cough/sputum production, physical findings compatible with pneumonia, fever > 38 $$^\circ{\rm C}$$, and new infiltrations on chest X-ray (CXR).Respiratory failure: Postoperative PaO_2_ < 8 kPa (60 mmHg) on room air, PaO_2_ / FiO_2_ (inspired fraction of oxygen) ratio < 40 kPa (300 mmHg), or arterial oxyhemoglobin saturation measured with pulse oximetry < 90% and requiring oxygen therapy.Pleural effusion: CXR with blunting of costophrenic angle, loss of sharp silhouette of the ipsilateral hemidiaphragm in upright position, displacement of adjacent anatomical structures, or (in supine position) hazy opacity in one hemithorax with preserved vascular shadows.Atelectasis: Lung opacification with mediastinal shift, hilum or hemidiaphragm shift towards the affected area, with compensatory hyperinflation in adjacent non-atelectatic lung.Bronchospasm: Newly detected expiratory wheeze treated with bronchodilators.Aspiration pneumonitis: Acute lung injury after inhalation of regurgitated gastric contents.Pneumonia: CXR with at least one of the following: infiltration, consolidation, cavitation; plus at least one of the following: fever > 38^。^C with no other cause, white cell count < 4 or > 12*10^9^ /L, > 70 yr of age with altered mental status with no other cause; plus at least two of the following: new purulent/changed sputum, increased secretions/suctioning, new/worse cough/dyspnea/tachypnoea, rales/bronchial breath sounds, worsening gas exchange.ARDS: Ventilated, bilateral infiltrates on CXR, PaO_2_:FIO_2_ < 300, minimal evidence of left atrial fluid overload within 7 days of surgery.Tracheobronchitis: Purulent sputum with normal chest radiograph, no intravenous (i.v.) antibiotics.Pulmonary oedema/Pulmonary congestion/hypostasis, acute oedema of lung, congestive heart failure, fluid overload.Exacerbation of pre-existing lung disease.

Patients conforming to one of the above conditions are deemed as positive for PPCs.

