### Intervention

For patients in both groups, one lung ventilation is initiated after readjusting the position of the double lumen tube in lateral decubitus position, The lumen to the independent lung remain closed to air during the interval between intubation to pleural opening. It’s opened to air for 2 min after pleural opening, and subsequently connected with the apneic oxygen insufflation device, which delivers pure oxygen to the independent lung at a constant rate of 5L/min. The dependent lung is ventilated in pressure-controlled volume-guaranteed (PCV-VG) mode, with a tidal volume of 4-5 ml/kg, I:E set to 1:2, and respiratory rate adjusted to maintain end-expiratory carbon dioxide within the range of 30-40 mmHg.

For patients in the study group, individualized PEEP titration is started right after the start of one lung ventilation. The initial PEEP is set to 15cmH_2_O. Subsequently PEEP is lowered at steps of 2cmH_2_O every 3 min. Before changing the level of PEEP, Cstat is calculated according to the formula (Cstat = VT/Pplat-PEEP). When Cstat ceases rising with the continuous lowering of PEEP but starts to drop, the previous PEEP level at which Cstat reaches its zenith is selected as the ideal PEEP (Fig. 2). Then PEEP is elevated to ideal PEEP and kept constant towards the end of the procedure.

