**Fig. 2 Fig2:**
[figure not shown]
Individualized PEEP titrated to maximize Cstat. *RM* ventilator driven recruitment maneuver, *PEEP* positive end expiratory pressure, *iPEEP* individualized PEEP, *Cstat* static lung compliance

For patients in the control group, PEEP is set to zero before pleural opening. Right after pleural opening, the dependent lung undergoes RM in pressure-controlled mode, driving pressure set to 20cmH_2_O, PEEP initially set to 5cmH_2_O and raised at steps of 5cmH_2_O and maintained for 10 breathing cycles for each step. When PEEP reaches 20cmH_2_O and plateau reaches 40 cmH_2_O, PEEP level is maintained for 15 breathing cycles towards the end of RM (Figs. 3 and 4), followed by iPEEP titration consistent with that of the study group.

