### Sample size calculations

The primary endpoint of this study is oxygenation index measured at T4. According to literature [16], oxygenation index for patients inhaling pure oxygen and under well oxygenated conditions during TLV usually ranges between 350-400 mmHg and drops to 150-200 mmHg after patients are switched to OLV. Therefore, during OLV, changes in oxygenation index within the limit of 50 mmHg would be clinically insignificant. Thus, the cut-off value for inferiority is set to 50 mmHg. In other words, in our study, if oxygenation index measured at T4 of the study group is below that of the control group, but the difference between that of the two groups is within 50, then the ventilation strategy of the study group is not inferior to that of the control group in terms of improving intraoperative oxygenation. We set probability of type 1 error at α = 0.025, probability of type 2 error at β = 0.20, and power value at 0.80; a sample size of 38 is calculated for each group by using PASS 11.0 software. Considering a 10% removal and dropout rate, a final sample size of 42 is required for each group.

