The pressure required to open up collapsed alveoli is far higher than that needed to prevent atelectasis formation. So, if PEEP is incrementally titrated, atelectasis usually develops before PEEP reaches the level sufficient to prevent alveoli from collapsing, and thus limits the benefits of PEEP. Spadaro and colleagues discovered that during one lung ventilation, PEEP obtained via both decremental and incremental titration procedures could reduce intrapulmonary shunt, but only PEEP titrated decrementally succeeded in reducing driving pressure and improving oxygenation [24]. Chuimello and colleagues found that during a stepwise decremental PEEP titration procedure, keeping PEEP constant for 5 min at each step was adequate for arterial partial pressure of oxygen, oxygenation index, venous admixture and arterial blood oxyhemoglobin saturation to reach equilibrium [23]. In contrast, during a stepwise incremental PEEP titration procedure, keeping PEEP constant for more than 60 min was insufficient for the aforementioned parameters to reach equilibrium [24]. In the majority of studies, during a PEEP titration procedure, iPEEP was selected based on parameters associated with oxygenation and respiratory dynamics. In addition, in numerous studies, PEEP was kept constant for 40 s to 3 min after each step of a stepwise decremental or incremental PEEP titration procedure, which was far shorter than the time required for paremeters including oxygenation index to reach equilibrium [4, 5, 14, 23]. In conclusion, acquiring PEEP from an incremental PEEP titration procedure is inappropriate.

One lung ventilation could result in injury of both the independent and the dependent lung [25]. According to literature, during one lung ventilation, apneic oxygen insufflation to the independent lung at a fixed rate of 5L/min could retain a degree of its expansion, which not only contributes to mitigated inflammatory reaction but also alleviates the anoxic-reoxygenation injury acquired after the end of one lung ventilation [26]. Therefore, we will apply apneic oxygen insufflation to the independent lung at a constant rate of 5L/min to minimize the effects of its injury on the incidence of PPCs. Although surgery-related lung injury is beyond control, according to literature, detriment caused by ventilator-associated lung injury is far greater than that caused by surgical trauma [27]. Thus, surgery-related lung injury has no profound impact on the outcome of this study.

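### The primary blood sample (T4) has a different trigger in each arm, so controls are sampled later after pleural opening whenever lung collapse is quick

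*Protocol article*

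**What the plan says.** The Sample size calculations section fixes the primary time point: "The primary endpoint of this study is oxygenation index measured at T4". The two arms are compared there against a non-inferiority margin of 50 mmHg.

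The Study endpoints section defines that time point by arm. For the study group it is "after achieving satisfactory collapse of the independent lung (lung collapse index reaching 8 [13]) (study group"; the definition then turns to the control group at "study group) and 5 min after completing iPEEP titration and achieving satisfactory collapse of the independent lung (control group) (T4". Both arms therefore require collapse of the operated lung. Only the control arm adds completed titration and a wait.

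The Intervention section places titration differently in the two sequences. In the study group "individualized PEEP titration is started right after the start of one lung ventilation", and the study-group definition of T3 puts the end of titration plus 5 min before the pleura is opened. In the control group "Right after pleural opening, the dependent lung undergoes RM in pressure-controlled mode", and titration follows the maneuver. The titration schedule is common to both: it starts at 15 cmH2O, and "Subsequently PEEP is lowered at steps of 2cmH_2_O every 3 min".

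No clock common to both arms (minutes since pleural opening, for instance) is set for T4. T5, before two-lung ventilation resumes, is defined in the same way for both arms.

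**The concern.** A between-arm comparison of a quantity that may change during surgery needs samples taken at comparable times. Here the time of the primary sample depends partly on the allocated arm, because the control rule carries conditions that take a minimum number of minutes after pleural opening and the study rule does not.

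The article itself gives reasons to think elapsed time could matter. The Sample size calculations section describes the index falling from 350-400 to 150-200 mmHg on the change to one-lung ventilation, and the Background describes atelectasis in the dependent lung as developing slowly. If the index drifts between the two sampling times, the drift is added to the treatment difference that is held against the 50 mmHg margin. It could make an inferior strategy look non-inferior, or hide a non-inferior one.

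**Working it through.** The article states no figure for the timing of T4, so the check builds it from the article's own steps.

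**Earliest control T4 after pleural opening**

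- Recruitment maneuver (Intervention): 10 breaths at each of PEEP 5, 10 and 15 cmH2O, then 15 at 20 cmH2O. 10 + 10 + 10 + 15 = 45 breaths. The rate is not stated; at an assumed 12 to 20 breaths/min this is 45/20 = 2.25 min to 45/12 = 3.75 min.
- Titration (Intervention): from 15 cmH2O downwards by 2, so at most 15, 13, 11, 9, 7, 5, 3, 1, which is 8 levels. At least 2 levels are needed to see compliance fall. At 3 min per level: 2 × 3 = 6 min to 8 × 3 = 24 min.
- Wait (Study endpoints): 5 min.
- Floor F = maneuver + titration + wait. Shortest: 2.25 + 6 + 5 = 13.25 min. Longest: 3.75 + 24 + 5 = 32.75 min.

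**Offset between arms for the same collapse time c (minutes from pleural opening)**

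Study T4 = c. For controls there are two readings of the text:

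- Reading A, the 5 min runs from titration only: T4 = max(c, F), so the offset is max(0, F − c).
- Reading B, the 5 min also runs from collapse: T4 = max(c, F − 5) + 5, so the offset is max(5, F − c).

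Example with 15 breaths/min (maneuver 3 min) and 5 levels (15 min), so F = 3 + 15 + 5 = 23 min. The collapse times are assumptions, because the article gives no expected value.

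| c | Study T4 | Control T4, A | Control T4, B | Since titration: study | Since titration: control, A / B |
|---|---|---|---|---|---|
| 10 | 10 | 23 | 23 | at least 15 | 5 / 5 |
| 20 | 20 | 23 | 25 | at least 25 | 5 / 7 |
| 30 | 30 | 30 | 35 | at least 35 | 12 / 17 |

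Fast collapse separates the arms on time since pleural opening. Slow collapse brings them together under reading A but leaves 5 min under reading B. Time since titration differs in every row.

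**Sensitivity of the test, as illustration only**

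The article does not state an SD. With margin 50, no true difference, one-sided 0.025 and power 0.80, n = 2 × (1.960 + 0.842)² × SD²/50² gives 37.2, rounded up to the stated 38, at SD 77. The standard error is then 77 × √(2/38) = 17.7 mmHg. The timing shifts below are assumed; the article gives no rate of drift.

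- A shift of 10 or 20 mmHg in favour of the study arm raises the chance of declaring non-inferiority at a true deficit of 50 from 2.5% to 8.2% or 20.4%.
- The same shift against it lowers power at no true difference from 81% to 62% or 40%.

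**The case against.** The strongest defence is that the two wordings are one rule applied to two sequences: final PEEP set, 5 min elapsed, operated lung collapsed. In the study arm the first two are already met before the pleura is opened, so only collapse needs to be named. On this view T4 matches the arms on physiological state, which is a reasonable choice. The Discussion also cites evidence that 5 min per decremental step is enough for oxygenation index to equilibrate, which supports the control wait. And since titrating before rather than after pleural opening is the strategy under test, no single sample can equalise both time since opening and time since titration.

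Much of this stands. Unequal time since titration is inherent in the comparison and is not a fault. It also follows that prescribing, for both arms, the later of collapse and 5 min after titration would change little: it would return the present study rule and keep the floor in controls. But matching on state does not match on minutes since pleural opening, and the equilibration evidence concerns PEEP steps, not time since pleural opening. A common clock from pleural opening is available, and the collapse condition can be kept alongside it.

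Two stronger readings are tempting and are not supported. A reader might infer that study T4 could be drawn while PEEP is still being stepped; the T3 definition puts the end of titration, plus 5 min, before pleural opening, so this would need a departure from the planned order. A reader might also infer that the arms differ in time to collapse because oxygen insufflation "could retain a degree of its expansion" of the operated lung; insufflation is the same in both arms, and the article offers no evidence of a differential effect.

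**Conclusion.** The point holds as a design weakness in the primary comparison. Control T4 has a floor of about 13 to 33 min after pleural opening, and study T4 has none. Sampling time is therefore tied to arm whenever collapse is faster than the floor, and always if the 5 min also runs from collapse. The floor rests on the article's step lengths, an assumed 12 to 20 breaths/min and 2 to 8 titration levels.

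How often collapse beats the floor is unknown, so no typical or maximum gap between arms can be quoted; a large figure would come only from pairing an assumed fast collapse with the longest titration. Nor does the article allow a statement that the result will be biased, by how much, or towards which arm. What can be said is that the offset is partly avoidable and affects the one comparison on which the non-inferiority claim rests.

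**What to change.** Use one T4 rule, on one clock, in both arms: for example, the later of a fixed time after pleural opening and collapse index 8. About 35 min would do for the fixed time, since it exceeds the 32.75 min that the longest control sequence needs. This also removes the doubt over where the 5 min starts.

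Record the actual minutes since pleural opening and the collapse index at each draw. The article already collects time from pleural opening to collapse index 8, but does not list the time of the T4 sample.

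Name oxygenation index at T5, already defined identically in both arms, as a supportive non-inferiority analysis with the same 50 mmHg margin.

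The cost is an amendment of one sentence, with no extra blood draw and no change in sample size. Patients already sampled under the present rule need a sensitivity analysis, and study-arm T4 will usually be drawn later than now. As under the present rule, T4 stays undefined for a patient who never reaches index 8 or who returns to two-lung ventilation first, so the amendment should say how such patients are handled.

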### Study visits and data collection

Patients are visited preoperatively, intraoperatively, and postoperatively on postoperative days 1 to 3 and at discharge (Table 1). We collect and record patients’ data at all the above-mentioned time points.Preoperative indicators: age, gender, height, body weight, BMI, ASA status, hypertension, diabetes, chronic hepatic illnesses, gastric esophagus reflux illness, long term use of steroids, history of obstructive sleep apnea (receiving CPAP therapy or not), smoking (current smoker/ have quitted smoking for more than 8 weeks), forced expiratory volume in the first second /forced vital capacity(FEV1/FVC), FVC, preoperative blood gas analysis( PaO_2_, PaCO_2_), hemoglobin, albumin, alanine aminotransferase (ALT), aspartate aminotransferase (AST), urea, creatine.Intraoperative indicators: Time required to achieve satisfactory lung collapse (lung collapse index reaching 8) from the moment of pleura opening, volume of blood loss, urine output, infusion volume (crystalloid fluid, colloid fluid), blood transfusion volume (heterotransfusion, autotransfusion), respiratory parameters (tidal volume, respiratory rate, plateau pressure, PEEP, driving pressure, Cstat, partial pressure of end-expiratory carbon dioxide, arterial blood oxygen saturation), hemodynamic parameters (blood pressure, heart rate, vasopressor), results of blood gas analysis, oxygenation index, Qs/Qt, duration of surgery, duration of anesthesia, duration of one lung ventilation, duration from placement in lateral decubitus position to pleura opening, side of surgery.Postoperative indicators: incidence of PPCs, length of hospital stay, incidence of ICU transference, length of ICU stay.Adverse events: adverse events will be monitored from the initiation of the trial intervention until discharge.

**Table 1 Tab1:**
[figure not shown]
Standard Protocol Items: Time schedule of enrollment, interventions, and assessments

*DLT* double lumen tube, *OLV* one lung ventilation, *POD1* post-operative day 1, *POD3* post-operative day 3, *RM* Recruitment maneuver, *PEEP* Positive end-expiratory airway pressure, Qs/Qt fraction of intrapulmonary shunt, *PPCs* Postoperative pulmonary complications, *ICU* intensive care unit

### Sample size calculations

The primary endpoint of this study is oxygenation index measured at T4. According to literature [16], oxygenation index for patients inhaling pure oxygen and under well oxygenated conditions during TLV usually ranges between 350-400 mmHg and drops to 150-200 mmHg after patients are switched to OLV. Therefore, during OLV, changes in oxygenation index within the limit of 50 mmHg would be clinically insignificant. Thus, the cut-off value for inferiority is set to 50 mmHg. In other words, in our study, if oxygenation index measured at T4 of the study group is below that of the control group, but the difference between that of the two groups is within 50, then the ventilation strategy of the study group is not inferior to that of the control group in terms of improving intraoperative oxygenation. We set probability of type 1 error at α = 0.025, probability of type 2 error at β = 0.20, and power value at 0.80; a sample size of 38 is calculated for each group by using PASS 11.0 software. Considering a 10% removal and dropout rate, a final sample size of 42 is required for each group.

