Numerous studies confirmed the advantages of iPEEP for patients undergoing one lung ventilation under general anesthesia [5, 12, 14, 15]. However, up till now, no consensus has been reached concerning the appropriate method for iPEEP titration. When tidal volume remains constant, driving pressure mainly correlates with Cstat; so PEEP could be titrated to maximize Cstat [15]. According to the result of a meta-analysis, the oxygenation of patients receiving driving-pressure-guided lung protective ventilation during one lung ventilation was significantly higher than those ventilated with other strategies [5]. Since increase in driving pressure strongly correlates with increased incidence of PPCs, we believe that for patients receiving one lung ventilation, titrating PEEP to optimize Cstat has its advantages.

This trial is going to test the hypothesis: the ventilation strategy of starting one lung ventilation and then iPEEP titration immediately after adjustment of the position of the double lumen tube in lateral decubitus position while not performing RM is not inferior to the strategy of initiating one lung ventilation right after pleura opening and then performing RM followed by iPEEP titration in the aspects of improving patients’ oxygenation, respiratory mechanics and reducing the incidence of PPCs during one lung ventilation.

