### Statistical analysis

The research team will cooperate with medical statisticians to analyze data after completing the trial. SPSS 20.0 software will be applied for data processing. Dropout or lost to follow up cases will be reported. Per-protocol analyses will be applied for all data. Under circumstances of missing values, multiple imputation shall be conducted. Kolmogorov–Smirnov analysis will be performed to discern normally distributed data. Normally distributed data will be presented as mean $$\pm$$ standard deviation (SD), while discrete data will be presented as median and interquartile range. Independent-samples T test will be adopted for univariate analysis of normally distributed data. Pearson correlation test will be used to test the linear relationship between two variables. Mann–Whitney U test will be applied for discrete data. Categorical variables will be expressed as relative risk ratio and assessed by Fisher’s exact test or chi-square tests, if applicable. 95% CI will be employed to express confidence level of all parameters. *P* value < 0.05 shall be defined as statistically significant.

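### The only written non-inferiority rule compares the measured T4 difference itself with 50 mmHg, and no confidence limit is tied to the margin, so the 0.025 error used for sizing is not controlled

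*Protocol article*

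**What the plan says.** **Hypothesis.** The Background of the protocol article frames the trial as non-inferiority: the strategy without recruitment "is not inferior to the strategy of initiating one lung ventilation right after pleura opening and then performing RM".

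**Endpoint, margin and error rates.** Under Sample size calculations, "The primary endpoint of this study is oxygenation index measured at T4" and "the cut-off value for inferiority is set to 50 mmHg". The same paragraph states "We set probability of type 1 error at α = 0.025, probability of type 2 error at β = 0.20, and power value at 0.80".

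**Decision rule.** That paragraph then restates the margin as a rule for the conclusion. If the study group's measured T4 value is below the control group's, "but the difference between that of the two groups is within 50, then the ventilation strategy of the study group is not inferior". No confidence limit and no test shifted by the margin is mentioned.

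**Analysis.** Under Statistical analysis, "Independent-samples T test will be adopted for univariate analysis of normally distributed data". Mann–Whitney is given for data called discrete, and a P "value < 0.05 shall be defined as statistically significant". A 95% CI is promised for all parameters. The section does not mention the margin, the figure of 0.025 or non-inferiority.

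**The concern.** A non-inferiority claim has to rule out, at the chosen error rate, that the new strategy is worse by the margin or more. Comparing the measured difference with the margin takes no account of sampling error. When the truth lies exactly at the margin, the estimate falls on the favourable side half the time.

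The analysis section does not repair this. Its tests address a difference of zero, so neither a significant nor a non-significant result answers whether a deficit of 50 mmHg has been excluded. The 95% CI would answer it, but nothing says that the interval is to be set against -50 mmHg.

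At stake is the trial's one primary conclusion. Followed as written, it could report that omitting the recruitment manoeuvre is not inferior when the omission truly costs the whole margin.

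**Working it through.** **Inputs from the protocol article:** margin 50 mmHg, alpha 0.025, power 0.80, 38 evaluable per group and 42 after dropout (Sample size calculations); 1:1 allocation (randomization section).

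**Assumptions, not in the article:** alpha is one-sided, the true difference used for sizing is 0, and the SD is common to both groups. No SD is stated.

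**1. The plan's own figure.** n per group = 2·SD²·(1.960 + 0.842)² / 50². Without an SD, 38 cannot be reproduced directly. Solving for the SD at n = 38 gives 50 / (2.802 × √(2/38)) = 77.8, and at n = 37 it gives 76.8. An SD just above 76.8 and up to 77.8 therefore rounds up to 38. A t-based calculation returns 38 at SD 76 to 76.5. Check with SD 77: 2 × 5929 × 7.849 / 2500 = 37.2, rounded up to 38. I use 77 as a working assumption and show a range.

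**2. The written rule at the margin.** If the true difference is -50, the estimate is centred on -50, so P(estimate > -50) = 0.50 for any SD and any n. Simulation with SD 50 to 150 and 38 or 42 per group gave 0.4975 to 0.501. That is 0.50 / 0.025 = 20 times the error used for sizing.

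**3. The written rule beyond the margin.** With 38 per group, SE = SD × √(2/38). At SD 77, SE = 17.7.
- True -60: P(estimate > -50) = P(Z > 10/17.7) = 0.29.
- True -75: P(Z > 25/17.7) = 0.08.

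**4. The rule based on a confidence limit.** Conclude non-inferiority if estimate - 1.993 × SE > -50 (t with 74 degrees of freedom). At SD 77 the half-width is 1.993 × 17.7 = 35.2, so the estimate must exceed -50 + 35.2 = -14.8. Error at a true difference of -50 is 2.5% for every SD tried (simulated 2.46% to 2.55%).

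| SD (assumed) | SE | Written rule passes at -50 / -60 / -75 | 95% CI rule passes at -50 / -60 / -75 | Estimate needed under CI rule | Power of CI rule at 0 |
|---|---|---|---|---|---|
| 50 | 11.5 | 50% / 19% / 1.5% | 2.5% / 0.2% / <0.01% | above -27.1 | 99% |
| 60 | 13.8 | 50% / 23% / 3.5% | 2.5% / 0.4% / 0.01% | above -22.6 | 95% |
| 77 | 17.7 | 50% / 29% / 8% | 2.5% / 0.6% / 0.04% | above -14.8 | 80% |
| 100 | 22.9 | 50% / 33% / 14% | 2.5% / 0.8% / 0.1% | above -4.3 | 58% |
| 150 | 34.4 | 50% / 39% / 23% | 2.5% / 1.2% / 0.4% | above +18.6 | 30% |

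**5. A case where the two sections disagree.** At SD 77, take an observed difference of -40. The 95% CI is -40 ± 35.2, that is -75 to -5, and the two-sided P against zero is about 0.03. The sample size section would call this not inferior. The listed t test would call the study group significantly worse. The interval runs well past -50, so non-inferiority is not shown.

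**The case against.** The strongest reply is that the sentence is an informal gloss. It sits in the sample size section and restates the cut-off just given. If the difference it speaks of is the true difference, it only states the hypothesis, and an alpha would be pointless under a rule with no inference. This is a possible reading. But the sentence speaks of the index as measured at T4, it states a conclusion, it is the only such rule in the article, and the analysis section does not correct it.

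A second reply is that the article is condensed and an analysis plan may state the confidence-limit rule. Had the article been silent, that would settle the matter. It is not silent: it prints a rule, and a plan using a confidence limit would contradict it.

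A reader might also infer stronger points that the document does not support:
- **Conflicting alphas.** Sizing at 0.025 and testing at 0.05 look inconsistent, but a two-sided 95% CI has 2.5% in each tail, so the two are compatible. The sizing alpha is also not called one-sided in the text.
- **A non-significant t test counted as proof of non-inferiority.** Nothing in the article says so. The tests are a general list by data type.
- **The primary endpoint sent to Mann–Whitney.** That test is assigned to discrete data. Using it for oxygenation index after a failed normality check is plausible, but it is an inference.
- **A sample size computed for another test.** The software procedure and the SD are not reported, so this cannot be established.

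**Conclusion.** The point holds as an error in what is written. The one stated decision rule, applied literally, gives a 50% chance of declaring non-inferiority at a true deficit of 50 mmHg, against the 0.025 used for sizing. This figure needs no SD and no sample size. It rests on reading the sentence as applying to measured values, which its wording favours.

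The other sizes depend on the SD, which the article does not give. With 77 mmHg back-solved from 38 per group, true difference 0 and one-sided 0.025, the rule passes about 29% of the time at -60 and 8% at -75. Over assumed SDs of 50 to 150 the ranges are 19% to 39% and 1.5% to 23%. At SD 77 the written rule accepts an observed shortfall of up to 50 mmHg, where a valid one would stop at about 15.

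This must be corrected before results are known, because over that span the choice of rule decides the verdict.

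**What to change.** State in both Sample size calculations and Statistical analysis that non-inferiority is concluded only if the lower limit of the two-sided 95% CI for the mean difference (study minus control) in oxygenation index at T4 is above -50 mmHg. Call the 0.025 one-sided if that is what was meant. Add that the tests of no difference do not decide the primary endpoint.

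The cost is a few sentences. No extra data are needed, and 38 per group still gives about 80% power if the SD is near 77 mmHg. A bootstrap interval as a sensitivity analysis is optional and not part of the correction.
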